## Abstract

**Background:**

Informed decision making is the theoretical basis in the UK for men's decisions about Prostate Specific Antigen (PSA) testing for prostate cancer testing. The aim of this study is to evaluate the effect of a web-based PSA decision-aid, *Prosdex*, on informed decision making in men. The objective is to assess the effect of *Prosdex *on six specific outcomes: (i) knowledge of PSA and prostate cancer-related issues – the principal outcome of the study; (ii) attitudes to testing; (iii) decision conflict; (iv) anxiety; (v) intention to undergo PSA testing; (vi) uptake of PSA testing. In addition, a mathematical simulation model of the effects of *Prosdex *will be developed.

**Methods:**

A randomised controlled trial with four groups: two intervention groups, one viewing *Prosdex *and the other receiving a paper version of the site; two control groups, the second controlling for the potential Hawthorn effect of the questionnaire used with the first control group. Men between the ages of 50 and 75, who have not previously had a PSA test, will be recruited from General Practitioners (GPs) in Wales, UK. The principal outcome, knowledge, and four other outcome measures – attitudes to testing, decision conflict, anxiety and intention to undergo testing – will be measured with an online questionnaire, used by men in three of the study groups. Six months later, PSA test uptake will be ascertained from GP records; the online questionnaire will then be repeated. These outcomes, and particularly PSA test uptake, will be used to develop a mathematical simulation model, specifically to consider the impact on health service resources.

**Trial registration:**

Current Controlled Trial: ISRCTN48473735.

## Background

*Prosdex *is a web-based decision aid to help men consider whether or not to have a Prostate Specific Antigen (PSA) test, potentially for prostate cancer [1]. It was developed in the context of the UK Prostate Cancer Risk Management Programme (PCRMP), a strategy, promoted by the UK National Cancer Screening Programme, which has, as one of its key goals, the promotion of informed decision making about PSA testing [2]. According to the strategy, men should only have a PSA test if they have received appropriate information and had the opportunity to make a decision – a decision which, for many, is difficult due to the uncertainty of prostate cancer testing. Despite its increasing incidence in men, the only widely-available test for prostate cancer, PSA, is limited not only by its poor sensitivity and specificity, but also by the uncertainty relating to the natural history and the management of the disease [2,3]. It is for these reasons that, unlike the USA, there is not a PSA screening programme in the UK. Moreover, the PCRMP strategy arguably reflects the tension between an evidence-based approach to population testing – PSA in this case – and the needs of individual men to make informed decisions about their own health.

Decision aids have been developed for a range of health conditions to facilitate informed decision making. Characteristically, the risks and benefits of different options are presented in a variety of formats and media, thereby helping patients in the process of values clarification, seen as fundamental for informed decision making. *Prosdex *was developed in 2002–04, supported by a grant from Cancer Research UK and the NHS Cancer Screening Programme [1]. Hosted by Cardiff University, with links from NHS Direct Online and Cancer Research UK, it presents evidence-based information about prostate cancer and PSA testing, encouraging users to weigh the pros and cons of testing for themselves. In addition, *Prosdex *includes video clips of enacted patient experiences about the PSA test and subsequent investigations/treatments. There is also information about 'shared decision making' and, through structured decision support (the 'decision stacker'), *Prosdex *aims to actively encourage informed decision making.

The aim of this proposed study is to evaluate the effect of *Prosdex *on informed decision making. In order to do so, a range of outcome measures need to be considered, due to the fact that a specific measure of informed decision making in PSA testing has not been developed. Three of the proposed outcome measures – knowledge, attitude to testing, and test uptake – are constituents of an informed decision making measure in another health context, prenatal Down syndrome [4]. These, and the other three proposed outcome measures – decision conflict, anxiety and intention to undergo testing – have been used in evaluations, specifically randomised controlled trials, of other PSA decision aids. In a systematic review of these trials, we found that knowledge increased by 19.5% and PSA testing decreased by 3.5% [5]. The six proposed outcome measures will, therefore, not only allow an assessment of the effect of *Prosdex *on informed decision making, but also will allow comparisons with other evaluations of PSA decision aids. This will hopefully enable an appraisal of implementation issues, for example the degree of awareness of the complexity surrounding PSA testing engendered in users by *Prosdex*[6]. Finally, a mathematical simulation model, using data from the trial, will allow extrapolations of the potential effects of *Prosdex *on health-service resource use, for example the impact on urological services, and on health outcomes.

## Methods

### i) Design

randomised controlled trial (RCT). This allows a comparison of the effect of a single intervention (*Prosdex*) on the specified outcomes in the objectives. The design employs four randomised groups of men in order to distinguish the effects of *Prosdex *from two other possible effects: format (electronic versus written), and the *Hawthorne *effect, specifically the effect that participating in a clinical trial could have on subsequent PSA uptake. RCTs have been used successfully to evaluate the effects of other PSA decision aids in North America [7,8].

### ii) Setting

Wales. Men recruited using GP lists.

### iii) Participants

#### a) Inclusion criteria

Men between 50 and 75 will be invited to participate, as prostate cancer is rare below the age of 50;[2] also, above the age of 75, men would be less likely, in our opinion, to complete the study, particularly the online questionnaire element. The men will access the study via the internet and must be able to use a computer. They will be asked to indicate this on the consent form. The numbers unable to participate due to this, in addition to those who fail to respond to the invitation, will be counted separately, in line with the CONSORT guidelines for reporting RCTs [9].

#### b) Exclusion criteria

Men who cannot read English will be excluded, as *Prosdex *was developed first only in English. Also excluded will be men who are known to have had prostate cancer and those whose GP records indicate that they have had a PSA test.

#### c) Recruitment process

Suitable men will be identified by GPs, in Wales, who will also send the invitation letters, participant information sheets (PIS) and consent forms. A member of the practice staff, probably the data manager, will be asked to identify men, aged 50–75, who have not had a PSA test. Using that generated list, the data manager will be asked to select 100 men using a serial recruitment process based on the date of the month of the men's birthdays: that is, the first man selected will be the first man on the list with a birthday 01/month/year; second man, 02/month/year; and so forth up to 31 when the process will be repeated until 100 men are selected. A member of the practice staff who has knowledge of the patients – Practice Manager or GP – will then be asked to screen the list for men who, in their opinion, are unsuitable for the trial due to serious ill-health. The number of men thus removed will be reported.

Affirmative consent forms from each practice will be transferred to the research officer who, in turn, will allocate each participant from that practice with a number provided the by trial statistician who will oversee the allocation process. Accordingly, the participants will be randomly allocated, by computer, to one of two intervention groups or to one of two control groups. This process will occur remotely in order to secure concealment. For each practice, the statistician will allocate 80 numbers, generated in 'blocks', the number for which will be between 12 and 16 in order to guarantee 'balance'. Randomisation will occur at the level of the man as we are interested in individual decision-making outcomes, and there is unlikely to be a significant intra-cluster correlation for these outcomes [10]. There will be no randomisation of the GP practices, but they will be stratified according to socio-economic groups, with an aim of 4 different such groups. After the collection of the data, there will be social analysis of these groups.

### iv) Intervention (see fig 1)

**Figure 1 F1:**
[figure not shown]
Intervention and control groups.

A specific version of the *Prosdex *website will be developed: it will require a password for access and will generate the online questionnaire. Men in intervention group 1 will be asked to log onto and view the website, either in their own homes or in another setting of their choice. The second intervention group (2) will receive a paper document comprising the text of the website. This enables evaluation of the Prosdex features (e.g. video clips and the structured decision support) that go beyond the mere presentation of the text content. In the first control group (A), men, after inserting their password, will be asked to complete the online questionnaire without viewing *Prosdex*. The second control group (B) will not initially be given the details of the study website.

There are, therefore, two main comparisons:

1) Intervention Group 1 v Control Group A:

*Prosdex *(+ online questionnaire) against no intervention, but with the online questionnaire: tests the effect of *Prosdex *content itself within the online context.

2) Intervention Group 1 v Intervention Group 2:

Two different formats to present almost identical content: tests the effects of the media: online versus paper-based.

The comparison between Control Group A and Control Group B allows a consideration of the *Hawthorne *effect of the questionnaire on PSA testing, to aid interpretation of outcomes in Intervention Groups 1 & 2.

At the six month stage, after the ascertainment of PSA testing status, men in the two intervention groups and control group A will be asked to repeat the online questionnaire. The purpose of repeating the questionnaire will be to evaluate any changes in the outcomes over time. Of particular interest is the effect on the principal outcome, knowledge, thereby allowing an assessment of knowledge retention. Men in control group B will also be asked at the six month stage to complete the online questionnaire in order to provide a control for the other three groups. All the men, therefore, at this six month stage, will be sent a letter asking them to access and complete the online questionnaire. This second questionnaire will have an additional question asking men to indicate, by 'left-clicking' on corresponding boxes, any types of information, newspapers/magazines for instance, they may have used in reaching a decision about how likely they are to have a PSA test.

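### The Prosdex versus paper comparison is given two incompatible purposes; it can estimate only the combined effect of online delivery, video clips and decision support

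*Protocol article*

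**What the plan says.** In the protocol article, Methods section iv) Intervention, group 1 views the Prosdex website. For the paper arm: "The second intervention group (2) will receive a paper document comprising the text of the website". The reason follows directly: "This enables evaluation of the Prosdex features (e.g. video clips and the structured decision support) that go beyond the mere presentation of the text content".

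The section then sets out its principal contrasts ("There are, therefore, two main comparisons"). The second is group 1 against group 2, described in these words: "Two different formats to present almost identical content: tests the effects of the media: online versus paper-based".

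Methods section i) Design makes the related claim that the four randomised groups are there to distinguish the effect of Prosdex from "two other possible effects: format (electronic versus written), and the *Hawthorne *effect".

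The Background section says what the website holds besides text. It "includes video clips of enacted patient experiences about the PSA test and subsequent investigations/treatments", and it offers structured decision support (the decision stacker), through which the site is meant to promote informed decision making actively.

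**The concern.** One contrast is given two purposes within a few lines. Under the first, the paper arm is a text-only comparator and the contrast shows what the extra website features add. Under the second, the arms carry nearly the same content and the contrast shows what the medium adds. If the content is nearly the same, there is little beyond the text to evaluate. If the extra features are the object of evaluation, the content is not nearly the same and the medium is not isolated.

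What is at stake is the meaning of one of the trial's two main comparisons. As written, the plan would permit a difference between groups 1 and 2 to be attributed to electronic versus written format, when the video clips or the decision support could have produced some or all of it. That matters to anyone deciding whether to put plain text online, to print it, or to invest in the interactive features.

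**Working it through.** The question is one of attribution, and no figure in the plan bears on it. The check sets the contents of the groups side by side and asks which effects their contrasts can identify.

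**Step 1: what each group receives before the first outcome assessment** (section iv) Intervention; Background for the website's contents)

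| Group | Website text | Online delivery of the text | Video clips | Structured decision support |
|---|---|---|---|---|
| Intervention 1 | yes | yes | yes | yes |
| Intervention 2 | yes | no (paper) | no | no |
| Control A | no | no | no | no |
| Control B | no | no | no | no |

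Control B differs from control A in not being given the study website at first, and so not answering the initial questionnaire. It serves the Hawthorne question and says nothing about medium.

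**Step 2: write the contrasts in terms of components.** Let T be the effect of the text on paper against nothing, M the change from putting that same text online, V the addition of the video clips and S the addition of the decision support. Let I collect any interactions among M, V and S. Then:

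- Group 2 v control A = T
- Group 1 v control A = T + M + V + S + I
- Group 1 v group 2 = (T + M + V + S + I) − T = M + V + S + I

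**Step 3: ask whether M can be recovered.** M appears only inside the sum M + V + S + I. The third contrast is the difference of the first two, so it adds no separate equation. To isolate M, the trial would need a group given the text online without video or decision support. To isolate S apart from the medium, it would need, for example, paper with decision support. Neither group exists. More participants would make the sum more precise but would not split it.

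**Step 4: compare with the two stated purposes.** The media purpose requires V + S + I to be zero or negligible. The features purpose, read as video and decision support alone, requires M (and I) to be negligible. The protocol supports neither assumption. It goes against the first by naming "video clips and the structured decision support) that go beyond the mere presentation of the text content" as what the comparison is there to evaluate.

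**The case against.** The strongest reply is that nothing is hidden. Section iv) states openly that group 2 gets text only and names the features it lacks, so a careful reader knows how the groups differ. The description of the content as similar is hedged. The word media could be taken loosely to mean a multimedia web package against print, since video and interactivity are things the web can deliver and paper cannot. On that reading the comparison is a reasonable pragmatic one between two whole packages.

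Part of this stands. The randomised contrast is valid for the package, and the disclosure is real. It does not rescue the stated interpretation. The protocol glosses media as online versus paper and, in the Design section, speaks of electronic versus written format. Structured decision support is not a medium, and the Background section presents it as an active part of the intervention. The disclosure is what brings the two purposes into conflict.

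A reader might be tempted to go further in four ways, which the document does not support:

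- **That the comparison lacks precision, or that the 20% relevant difference is wrong for it.** Section (vi) Comparisons and analysis does not tie the 20% to group 1 v group 2, and precision has no bearing on attribution.
- **That a non-significant result will be read as showing that format does not matter.** The protocol makes no equivalence claim.
- **That interval estimates are missing.** Section (vi) already promises them.
- **That group 2 answers the knowledge questions with the printed text to hand while group 1 does not.** The article does not say what either group may consult while answering, so that asymmetry would be an assumption.

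**Conclusion.** The point holds as an error in what the second main comparison is said to show. Group 1 v group 2 identifies one quantity: the joint effect of online delivery, video clips and structured decision support over the same text on paper. It does not identify an effect of medium or format alone, so the design lacks that property claimed for it in sections i) and iv).

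The reach is limited. One of the two main comparisons is affected, and only in its interpretation. Allocation, group sizes, power statement and analysis methods are untouched, as are the comparisons of group 1 with control A and of control A with control B. The conclusion rests on the paper document being text only, as section iv) says, and on the four groups described being the only ones. It does not depend on any effect size or standard deviation.

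**What to change.** Reword two places in the protocol article.

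1. **Section iv) Intervention, comparison 2.** Replace the statement that it tests the media with wording such as: this comparison estimates the effect of the full Prosdex website (online delivery, video clips and structured decision support together) over its text on paper; no conclusion about medium or format alone will be drawn. Drop the description of the two arms as near-identical in content, and read the earlier sentence on features beyond the text in the same combined sense.
2. **Section i) Design.** Replace the claim that the four groups separate out a format effect with the same combined description. Leave the Hawthorne claim as it is.

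The cost is a change of wording and a narrower claim, with no new group, participants or analysis. If an effect of medium alone is truly wanted, it would need a further group given the text online without video or decision support. That is a larger change, and correcting the present claim does not require it.

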#### e) Intention to undergo PSA testing

This will be assessed using a single item question, with Likert-like response scale, which has also been used in our earlier evaluation of a brief paper-based leaflet about PSA testing [12].

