#### f) Uptake of the PSA test

This will be assessed at six months after the intervention. GPs who participate in the study will be asked to ascertain the men's PSA testing status for that six month period, from their records, and inform the research team whether or not the test was done. The GPs will be provided with specific forms for this purpose, to be returned to the research team. It is possible that men may have had PSA tests elsewhere, such as via hospital clinics, but it is likely that these will be evenly distributed across the intervention and control groups. Moreover, it may be less likely that these decisions to be tested were patient-led. Such 'external' results, when they do occur, are increasingly recorded in GP records.

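### The six-month questionnaire repeats the intention item to men already tested, with no described rule for them, and tests absent from GP records go unchecked

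*Protocol article*

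**What the plan says.** All references are to the Protocol article.

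- **Who gets the repeat, and when** (section iv, Intervention). Once GPs have reported testing status at six months, groups 1, 2 and A "will be asked to repeat the online questionnaire". Control group B completes it for the first time at this point. The section then covers everyone: "All the men, therefore, at this six month stage, will be sent a letter asking them to access and complete the online questionnaire". Nothing limits this to untested men.
- **Why it is repeated** (same section). "The purpose of repeating the questionnaire will be to evaluate any changes in the outcomes over time", with knowledge retention singled out as the main interest.
- **What is added** (same section). "This second questionnaire will have an additional question asking men to indicate" the information sources "they may have used in reaching a decision about how likely they are to have a PSA test". No other addition is described.
- **What it carries** (section v, Outcomes). Five of the six outcomes come from this questionnaire, including decision conflict and intention. On intention: "This will be assessed using a single item question", answered on a Likert-like scale.
- **Uptake** (section f). GPs report testing status for the six months from their own records. The article accepts that tests may be done elsewhere and says "it is likely that these will be evenly distributed across the intervention and control groups". It adds that such tests may less often be the man's own decision, and that outside results now reach the GP record more often.
- **Use of uptake** (section vii). Uptake is the main trial input to the simulation model of workload and resources.

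**The concern.** Intention to have a test means one thing for an untested man and something else for a man tested a month ago. The second man may have held the strongest intention of all, acted on it, and now answer that a further test is unlikely. Scored as it stands, he appears to have lost his intention. If testing differs between groups, the group that tested more gets more of these artificially low scores, so the artefact runs against the uptake result. If Prosdex lowers testing, as the review cited in the Background found for other aids, its intention score would be pulled down less than the control group's. A true fall in intention could be partly hidden.

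The second issue is how completely uptake is captured. Where a man goes for a test is decided after allocation, by men who know whether they received the aid. Randomisation balances what men bring to the trial. It does not guarantee balance in where they later seek testing or in whether the result reaches the GP. Even if capture is balanced, missed tests shrink the difference and lower the absolute uptake that feeds the model. Every man is contacted at six months, so the assumption could be checked directly, but no such check is described.

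**Working it through.** **Inputs from the article.** 150 men per group. For decision conflict, a 0.32 SD shift is said to be detectable with 80% power at 5% alpha (section vi). PSA testing fell by 3.5% in the systematic review (Background), read here as 3.5 percentage points.

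**Inputs that are assumptions.** The article gives no number of response categories, SD, uptake rate or capture rate. I assume a 5-point intention item with SD 1.2. Uptake and capture are varied below.

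**1. The plan's own figure.** With two-sided alpha, the shift detectable at 80% power is (1.960 + 0.842) × √(2/150) = 0.3235 SD. Power at 0.32 SD is Φ(0.32/√(2/150) − 1.960) = Φ(0.811) = 79.1%. The stated figure reproduces. It is given for decision conflict and serves below only as a yardstick.

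**2. Intention, contrast between groups.** Spurious shift = (difference in proportion tested) × (fall in a tested man's answer). Dividing by 1.2 gives SD units.

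| Uptake difference | Answer falls by 4 (5 to 1) | Answer falls by 2 |
|---|---|---|
| 3.5 points | 0.035 × 4 = 0.14 (0.12 SD) | 0.07 (0.06 SD) |
| 5 points | 0.20 (0.17 SD) | 0.10 (0.08 SD) |
| 10 points | 0.40 (0.33 SD) | 0.20 (0.17 SD) |

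A fall of 4 in every tested man is the most that a 5-point item allows. At the 3.5-point difference, 0.14 is therefore the ceiling.

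**3. Intention, change over time (groups 1, 2 and A).** Here the artefact scales with the whole proportion tested, not the difference. With a fall of 4 and uptake of 2%, 5% or 10%, mean intention drops by 0.08, 0.20 or 0.40 points (0.07, 0.17 or 0.33 SD). With a fall of 2, these halve.

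**4. Uptake, balanced under-capture.** Observed difference = capture × true difference. At 90%, 80% and 70% capture, 3.5 points becomes 3.15, 2.8 and 2.45. Absolute uptake shrinks by the same factor: a true 10% is recorded as 8% at 80% capture.

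**5. Uptake, unbalanced capture (hypothetical).** With true uptake of 10% in both groups and capture of 90% v 70%, recorded uptake is 9% v 7%, a false difference of 2 points. The standard error of a 150 v 150 difference at 10% is √(2 × 0.1 × 0.9/150) = 3.5 points, so this is about 0.6 standard errors. The article holds no evidence that capture differs.

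**6. Decision conflict.** If tested men's scores differ by 0.5 to 2 SD and 3.5 points more are tested in one group, the contrast moves by 0.035 × 0.5 = 0.018 to 0.035 × 2 = 0.07 SD. This is small beside 0.32 SD.

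**The case against.** Several stronger readings are tempting, and the article does not support them.

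- **That the questionnaire never asks about testing.** The article does not print the items. It describes one addition and does not say that it is the only change. The phrase about how likely men are to be tested is a summary of that item, not necessarily its wording. What can be said is that no such item is described.
- **That the six-month scores mislead.** GP-recorded status is obtained before the repeat, so most tested men can be identified at analysis, and a rule for them could sit in an analysis plan that is not shown. This weakens the point without removing it. GP status is given no described role in routing, and no analysis plan can recover an answer that was not collected.
- **That decision conflict is meaningless after a test.** Section c describes the scale as measuring whether a man feels his choice is the best one for him. That can still be read once the choice is made, so the difficulty lies with intention.
- **That all tests outside the practice are missed.** Section f says outside results increasingly reach the GP, and suggests that such tests may less often be patient-led, which would limit an aid's influence on them. The loss is confined to tests never entered in the record.

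The size is also modest. The 0.12 SD is a worst case on assumed inputs, and knowledge retention is the main reason for the repeat. What stands is an ambiguous intention score for tested men and a balance assumption that is reasoned but left unchecked.

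**Conclusion.** The point holds as a minor one. As described, the repeat asks tested men an intention question whose answer is ambiguous, and no handling is given. The likely distortion of the group contrast is at most about 0.12 SD at the review's 3.5-point uptake difference. It is less with a smaller response shift and more if uptake differs more widely. Change over time is more exposed, because it depends on total uptake, which the article does not give. For uptake, tests absent from GP records attenuate the difference in proportion to capture and lower the model's input even when the loss is balanced. Unbalanced loss is possible but not shown.

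These sizes rest on the assumed item format, SD, response shift and capture rates. The principal outcome, the sample size and every comparison from the first questionnaire are untouched.

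**What to change.** 1. Add one opening item to the six-month questionnaire for all four groups: 'Have you had a PSA test since joining the study? If yes, where?'
2. Route men who report a test past the intention item.
3. Analyse six-month intention for all randomised men, with tested men (GP record or self-report) placed in the highest intention category. State how non-responders are handled. Otherwise a tested non-responder gets a score from the GP record while an untested one is simply missing.
4. Keep GP records as the main source for uptake. Add a sensitivity analysis that counts a test if it appears in the GP record or in self-report, over the same six months.
5. Keep decision conflict in all men as the main six-month comparison. Any split by tested status is descriptive only, because it conditions on something that happens after randomisation and that the aid may change.

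The cost is one item in a questionnaire that is already being modified and sent to every man, plus one sensitivity analysis. The downsides are recall error and non-response in self-report, which is why GP records stay primary. Placing tested men in the top category is also a convention, and may overstate intention where the test was not the man's own choice.
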